#### **2. Rational and background information:**

Gestational diabetes mellitus (GDM) is defined as any glucose intolerance first recognized in pregnancy [1]. According to the International Association of Diabetes in Pregnancy Study Group (IADPSG), the global prevalence of GDM is 14%, with a regional prevalence of 7% in North America, 10.4% in Europe, and 27.6% in the Middle East and North Africa [2]. According to a systematic review including 24 studies and 1011 participants, the prevalence of GDM in Iran which is located in the Middle East was 3.41%, with the highest and lowest prevalence of 18.6% and 1.3%, respectively [3].

GDM has maternal and fetal consequences. For example, women affected with GDM are in a greater risk of pre-eclampsia, cesarean section, and birth canal trauma due to macrosomia [4]. If GDM happens at the time of fetal organogenesis, the rate of congenital abnormalities and abortion will increase [5]. Fetal macrosomia, shoulder dystocia, and hypoglycemia at birth are some neonatal short-term consequences. In addition, childhood and adulthood obesity, increased risk of diabetes in later life, and cardiometabolic disorders are some examples of long-term consequences of GDM [6]. Pre-conception screening tests for glucose intolerance and counseling should be considered as preventive measures [7].

Education of pregnant women plays an important role in management of GDM. It can improve the compliance of women with lifestyle change or medication and decrease maternal and neonatal consequences of GDM [8].

**3. Study objectives:** The primary aim of the current study is to evaluate the effect of education through mobile app on lifestyle of women with gestational diabetes, and the secondary aim is to assess the effect of this intervention on blood sugar.

4. Study design: This study will be a parallel randomized controlled trial.

**Inclusion/exclusion criteria:** Women will be eligible to participate in this study if they: have gestational diabetes (high FBS and abnormal two-hour fasting glucose tolerance test using 75 gr glucose), are at gestational age of 24-28 wks, have basic literacy, have a smart phone, are gravida 1 or 2, and will receive low or moderate scores from Health Promoting Lifestyle Questionnaire. Women will be excluded from the study if they have overt diabetes or will be affected with pre-eclampsia or hypertension. We expect that data collection will take 1 year.

Setting: The pregnant women with GDM who will attend to the Public Health Center No 1 in Baghmalek, Khuzestan province, Iran will be recruited according to the inclusion criteria. The laboratory of this health center will be used for all blood tests.

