The first section will be included information about gestational diabetes, its definition, symptoms and consequences, and ways of monitoring blood sugar. In the second section, the user will be provided with information about increasing patients' awareness of the importance of following a diet, choosing the right foods, recommendations for healthy cooking, suggestions for meals and snacks, different methods to get more fruits and vegetables, foods that diabetic patients should avoid, and ways to deal with overeating.

The third section will be dealt with proper posture habits while standing, correct sitting posture, how to sit on the floor, sleeping on one side, getting up from sleep, and picking up objects.

In the fourth section that will be dedicated to exercise and physical activity, the user will be provided with information about increasing patients' knowledge of the health benefits of regular physical activity, types of suitable physical activities during pregnancy, the amount of exercise recommended per day, the benefits of walking, and the correct walking techniques. The fifth section will be concerned with ways of and recommendations for increasing spiritual growth, improving interpersonal relationships, increasing responsibility, and stress management.

In the sixth section, the ways of contact with the researcher and software designer in case of any problem in the software or questions about how to use the software will be explained.

Recommendations will be introduced in the seventh sections, and other related programs will be introduced in the eighth section. It should be noted that in order for a better understanding of the educational materials, attractive and relevant images will be used in each section.

After the software will be installed on the mobile phone of the mothers in the intervention group, the intervention will be started.

Also, the researcher will follow the participants in the intervention group at least twice a week through phone calls or text messages, and if there will any ambiguity, the necessary explanations will be provided for a better understanding of the educational items. In addition, in order to better follow up and control the mothers, a group will be formed in WhatsApp by the researcher. Also, the contact number of the researcher will be provided to the participants from the very beginning of the intervention, so that they can call privately and solve their problems.

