For the control group, routine health care will be provided by a midwife. In Iranian health centers, educational pamphlets are provided for mothers with diabetes, and necessary health recommendations regarding diet, regular physical activity to control blood sugar will be made.

**6. Safety considerations:** All blood tests will be collected in the laboratory of Health center No 1 in Baghmalek, Iran, by a trained nurse.

**7. Follow-up:** Fasting blood sugar (FBS) and blood sugar 2 hours after meal will be measured at the beginning of the study and 4 weeks after intervention. Also, participants will be asked to complete HPLP questionnaires at the beginning of the study and four weeks thereafter.

**8. Data management and statistical analysis:** All data will be analyzed using SPSS version 25.

The Chi-square test (or Fisher's Exact test), and independent t-test (or Mann-Whitney test) will be used for categorical and continuous data, respectively. ANCOVA will be used for comparing

blood sugar and HPLP between two groups controlling for baseline.  $P < 0.05$  will be considered statistically significant.

**9. Quality assurance:** All laboratory tests will be done in a reference laboratory. Diagnosis of GDM will be done according to high fasting blood sugar and abnormal two-hour fasting glucose tolerance test using 75 gr glucose.

10. Expected outcomes of the study: Primary outcomes: Health promoting lifestyle

Secondary outcomes: Blood sugar

**11. Dissemination of results and publication policy:** The results of the study will be published in a scientific international journal. Also, the summary of the study will be accessible for all pregnant women in a simple language.

**12. Duration of the project:** Sampling is expected to take six months. Data analysing, interpretation, and writing the paper needs six months.

**13. Anticipated problems:** Some women may refuse to attend the clinic due to the COVID-19 pandemic. In this regard, face masks will be distributed free of charge to the participants and social distancing will be maintained.

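### The exclusion criterion, as worded, permits removal of randomised women who later develop pre-eclampsia or hypertension; it should apply only to conditions present at or before randomisation

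*Protocol*

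**What the plan says.** The study design section of the protocol states: "This study will be a parallel randomized controlled trial". Women are eligible if they "are at gestational age of 24-28 wks", among other criteria. The exclusion sentence in the same paragraph reads: "Women will be excluded from the study if they have overt diabetes or will be affected with pre-eclampsia or hypertension".

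The follow-up section fixes the time of the primary outcome: "participants will be asked to complete HPLP questionnaires at the beginning of the study and four weeks thereafter". Blood sugar, the secondary outcome, is measured at the start and four weeks after the intervention. The analysis section plans ANCOVA of both outcomes, controlling for baseline.

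The background section says that "women affected with GDM are in a greater risk of pre-eclampsia, cesarean section" and other complications, and that educating pregnant women can "decrease maternal and neonatal consequences of GDM".

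The intervention section adds a difference in contact between arms: "the researcher will follow the participants in the intervention group at least twice a week through phone calls or text messages". Control women receive routine care from a midwife.

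No section limits the exclusion to the time before randomisation. None says that a woman who develops one of these conditions on study is still followed and analysed.

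**The concern.** A condition present at entry is an ordinary eligibility matter. A condition that arises after randomisation is different, because whether it occurs, or is noticed, may depend on the arm. If such women are taken out, those who remain are no longer the groups that randomisation formed. The ANCOVA then compares women who stayed free of a complication under each allocation.

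Two things are at stake. The first is bias, if the women removed differ between arms in number or in kind. The second is loss of data. The rule speaks of exclusion from the study, not from one analysis, so the four-week outcomes of these women may never be collected. A later analysis plan could not recover them.

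**Working it through.** **1. Can the event fall between randomisation and outcome?** Entry is at 24-28 weeks of gestation and the lifestyle questionnaire is repeated four weeks after the start. The primary outcome therefore falls at 24 + 4 = 28 to 28 + 4 = 32 weeks. Nothing in the protocol rules out new pre-eclampsia or hypertension in that interval, and the background section names pre-eclampsia as a risk of the disease under study.

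**2. Can the event depend on the arm?** The protocol names pre-eclampsia as a consequence of gestational diabetes and says that education can reduce such consequences. On that rationale the app could change who is removed. Contact at least twice a week in one arm only could also change how often the event comes to light. The first route would leave more events in the control arm. The second would show more in the intervention arm.

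**3. How large could the distortion be?** The protocol shown states no event rate, SD, effect size or sample size, so there is no figure to reproduce. Everything below is an assumption made for illustration.

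Let *p* be the share removed in an arm (T intervention, C control), and let *d* be the number of SDs by which the mean outcome of removed women lies below that of retained women. A higher score is better. In each arm the retained mean equals the full mean plus *p × d*. Hence

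bias = (difference among retained women) − (difference among all randomised women) = *p_T × d_T − p_C × d_C*.

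| p_C | p_T | d_C | d_T | Calculation | Bias (SD) |
|---|---|---|---|---|---|
| 2% | 1% | 0.5 | 0.5 | 0.005 − 0.010 | −0.005 |
| 5% | 2% | 1 | 1 | 0.02 − 0.05 | −0.03 |
| 10% | 5% | 1 | 1 | 0.05 − 0.10 | −0.05 |
| 15% | 5% | 1 | 1 | 0.05 − 0.15 | −0.10 |
| 5% | 5% | 1 | 1 | 0.05 − 0.05 | 0 |
| 5% | 5% | 0.5 | 1 | 0.05 − 0.025 | +0.025 |
| 5% | 10% | 1 | 1 | 0.10 − 0.05 | +0.05 |
| 5% | 10% | 0.5 | 1 | 0.10 − 0.025 | +0.075 |

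A negative value makes the app look worse than it is; a positive value makes it look better. For blood sugar, where lower is better, the sign reverses but the interpretation does not. The bias is zero only if *p_T × d_T = p_C × d_C*. Equal event rates alone do not ensure that.

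**4. A second model as a cross-check.** Suppose that a latent liability to the event has correlation ρ with a poor outcome, and that a woman is removed when the liability exceeds the cut-off *c* that gives the assumed event rate. The retained mean shifts by ρ × φ(c)/Φ(c).

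- 15% against 5%: φ/Φ is 0.2743 and 0.1086, a difference of 0.1657. With ρ = 0.24 the shift is 0.040 SD; with ρ = 0.5 it is 0.083 SD.
- 10% against 5%: 0.1950 − 0.1086 = 0.0864. With ρ = 0.24 the shift is 0.021 SD.
- 2% against 1%: 0.0494 − 0.0269 = 0.0225. With ρ = 0.24 the shift is 0.005 SD; with ρ = 0.5 it is 0.011 SD.

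If the larger rate is in the control arm, these shifts again dilute the app effect. Both models give the same order of magnitude.

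**5. What baseline adjustment does.** These figures are for unadjusted outcomes. ANCOVA takes out the part of the link between event and outcome that runs through the baseline value. The part that baseline does not explain remains.

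**The case against.** The strongest reply is that the sentence may be about eligibility only. It stands under the inclusion and exclusion criteria and does not mention randomisation or withdrawal. The inclusion sentence just before it makes the same change of tense for a pure screening item, the lifestyle questionnaire score, and the protocol uses the future tense loosely throughout. A reader might infer that the protocol definitely removes women after randomisation and that the randomised comparison is therefore broken. The text does not go that far. What remains is that the sentence sets a present condition against a later one and excludes from the study, and that no other section closes the door on later removal.

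The second reply is that the effect may be negligible. With four weeks between baseline and primary outcome, events may be few, and at 2% against 1% the shift is about 0.005 SD. This stands as a comment on size. The larger figures rest on event rates and differences between arms for which the protocol gives no basis.

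The third is that analysis sets belong in an SAP, which was not available here. This answers the point only in part, because the rule as written can stop follow-up, and an SAP cannot restore outcomes that were not collected.

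**Conclusion.** The point holds as a fault of wording with a possible consequence for bias. The criterion most naturally covers, and at the least permits, removal of randomised women for an event that the protocol ties to gestational diabetes and, through its rationale for education, possibly to the arm.

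Size and direction cannot be determined from the documents. Over the assumed inputs the distortion runs from about 0.005 SD to about 0.1 SD in absolute size, and it can be zero.

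Two stronger conclusions are tempting and are not supported. One is that the rule would favour the app: if more control women with poor outcomes are removed, it dilutes the app effect, and it favours the app only in cases such as greater detection in the intervention arm. The other is that adjustment for baseline does nothing: it removes the part explained by baseline and leaves the rest.

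The case for a change therefore rests on the principle of keeping randomised women in the comparison and on the low cost of doing so, not on a demonstrated large bias.

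**What to change.** Replace the exclusion sentence with wording such as:

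*A woman is not eligible if overt diabetes, pre-eclampsia or hypertension is present at or before randomisation. Women in whom pre-eclampsia or hypertension develops after randomisation remain in follow-up where outcomes can be obtained and are analysed in the arm to which they were allocated. Known events are reported by arm.*

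An analysis without these women should be a sensitivity analysis at most. Any clinical decision to stop the intervention should be worded separately from removal from follow-up and analysis, so that one does not imply the other.

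The cost is small but not nil. A few more women are followed to the four-week visit, and the events need a place on the data form. The protocol describes its checklist for blood sugar results and describes no blood-pressure measurement, so it should also say how events come to be known, in the same way for both arms.

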#### 4. Methodology

Instruments: A demographic and obstetric information questionnaire (including questions about age, gravidity, number of children, gestational age, body mass index, educational attainment, occupation, and intended pregnancy) will be used for gathering data. The content validity of this questionnaire will be confirmed. The results of blood sugar tests will be recorded in a checklist. Furthermore, the Health Promotion Lifestyle Profile (HPLP-II) will be used for gathering data about lifestyle of women. This questionnaire has 52 questions in 6 dimensions including spiritual growth and self-actualization (11 questions), responsibility for health (13 questions), interpersonal relationships (8 questions), stress management (6 questions), sports and physical activities (7 questions) and nutrition (7 questions). The questionnaire is scored based on a 4-items Likert scale (never=1, sometimes=2, often=3, and always=4). The minimum score is 52 and the maximum is 208. The total score is categorized into three levels: a score less than 103 represents a poor lifestyle, 104-155 indicates an average lifestyle, and a score of  $\geq 156$  shows a good lifestyle [9]. The psychometric evaluation of the Persian version of this questionnaire was done by Mohammadi-zeidi et al [10]. In the Persian version, three questions were removed because of low factor load, and the number of questions reduced to 49.

**Intervention:** The mobile phone app will be developed by one of the researchers (DR) as following: First, the content of the teaching material will be determined according to six dimensions of HPLP including (nutrition and diet, physical activity and exercise, responsibility, interpersonal relationship, spiritual growth, and stress management). The mobile application will

be designed using coding and multimedia program for the mobile operating system Android 4 and above. The application will be evaluated by the research team. For the pilot study, the alpha version of the application will be sent to 10 faculty members of the Midwifery Department, and its flaws will be removed. Finally, the beta version will be used for implementation in the intervention group. The educational application will be included 8 sections as follows: gestational diabetes, nutrition, physical posture, exercise, advice, contact with us, and other programs.

The first section will be included information about gestational diabetes, its definition, symptoms and consequences, and ways of monitoring blood sugar. In the second section, the user will be provided with information about increasing patients' awareness of the importance of following a diet, choosing the right foods, recommendations for healthy cooking, suggestions for meals and snacks, different methods to get more fruits and vegetables, foods that diabetic patients should avoid, and ways to deal with overeating.

The third section will be dealt with proper posture habits while standing, correct sitting posture, how to sit on the floor, sleeping on one side, getting up from sleep, and picking up objects.

In the fourth section that will be dedicated to exercise and physical activity, the user will be provided with information about increasing patients' knowledge of the health benefits of regular physical activity, types of suitable physical activities during pregnancy, the amount of exercise recommended per day, the benefits of walking, and the correct walking techniques. The fifth section will be concerned with ways of and recommendations for increasing spiritual growth, improving interpersonal relationships, increasing responsibility, and stress management.

In the sixth section, the ways of contact with the researcher and software designer in case of any problem in the software or questions about how to use the software will be explained.

Recommendations will be introduced in the seventh sections, and other related programs will be introduced in the eighth section. It should be noted that in order for a better understanding of the educational materials, attractive and relevant images will be used in each section.

After the software will be installed on the mobile phone of the mothers in the intervention group, the intervention will be started.

Also, the researcher will follow the participants in the intervention group at least twice a week through phone calls or text messages, and if there will any ambiguity, the necessary explanations will be provided for a better understanding of the educational items. In addition, in order to better follow up and control the mothers, a group will be formed in WhatsApp by the researcher. Also, the contact number of the researcher will be provided to the participants from the very beginning of the intervention, so that they can call privately and solve their problems.

For the control group, routine health care will be provided by a midwife. In Iranian health centers, educational pamphlets are provided for mothers with diabetes, and necessary health recommendations regarding diet, regular physical activity to control blood sugar will be made.

**6. Safety considerations:** All blood tests will be collected in the laboratory of Health center No 1 in Baghmalek, Iran, by a trained nurse.

**7. Follow-up:** Fasting blood sugar (FBS) and blood sugar 2 hours after meal will be measured at the beginning of the study and 4 weeks after intervention. Also, participants will be asked to complete HPLP questionnaires at the beginning of the study and four weeks thereafter.

**8. Data management and statistical analysis:** All data will be analyzed using SPSS version 25.

The Chi-square test (or Fisher's Exact test), and independent t-test (or Mann-Whitney test) will be used for categorical and continuous data, respectively. ANCOVA will be used for comparing

blood sugar and HPLP between two groups controlling for baseline.  $P < 0.05$  will be considered statistically significant.

**9. Quality assurance:** All laboratory tests will be done in a reference laboratory. Diagnosis of GDM will be done according to high fasting blood sugar and abnormal two-hour fasting glucose tolerance test using 75 gr glucose.

10. Expected outcomes of the study: Primary outcomes: Health promoting lifestyle

Secondary outcomes: Blood sugar

**11. Dissemination of results and publication policy:** The results of the study will be published in a scientific international journal. Also, the summary of the study will be accessible for all pregnant women in a simple language.

**12. Duration of the project:** Sampling is expected to take six months. Data analysing, interpretation, and writing the paper needs six months.

**13. Anticipated problems:** Some women may refuse to attend the clinic due to the COVID-19 pandemic. In this regard, face masks will be distributed free of charge to the participants and social distancing will be maintained.

**14. Project management:** All authors were involved in the conception of the study. [name] will develop the mobile app. [name] will collect the data. [name] received the expenses. [name] and [name] will supervise the research process. [name] will analyze the data. All authors will be responsible for data interpretation. [name] will be responsible for writing the first draft of the manuscript.

**15. Ethics:** This research will be performed in line with the principles of the Declaration of Helsinki. Approval was granted by the Ethics Committee of Ahvaz Jundishapur University of Medical Sciences (Ref. No: IR.AJUMS.REC.1399.076). Also, the protocol was registered in

the Iranian Registry for Clinical Trials (Ref. No: IRCT20200817048434N1). Written informed consent will be obtained from eligible women.

**16. Budget:** Ahvaz Jundishapur University of Medical Sciences will provide the expenses of the research.

**17. Supplementary support for the project:** For this project, we anticipated that except for expenses that receive from Ahvaz Jundishapur University of Medical Sciences, we will not receive any fees from anywhere else.

**18. Collaboration with other researchers of institutions:** All researchers in this project are affiliated with Ahvaz Jundishapur University of Medical Sciences and we do not anticipate collaborating with other researchers in other institutions.

